### Randomization and blinding

Random allocation of eligible participants was conducted in two stages, and in order to offer participants a service that was geographically accessible they were asked to indicate the suburbs where they would prefer to see an EP. First, eligible patients were randomly assigned in a 1:2 ratio to the usual care group or to the intervention group using a randomized block design stratified by participant gender with block sizes of 6. Second, those allocated to the intervention group were randomly assigned in a 1:1 ratio to face-to-face only or face-to-face and telephone counseling using a randomized block design stratified by participant gender and the suburb location of the EP, using block sizes of 6. The randomization process occurred on computer at a centralized location by an independent statistician. Participants were notified of group allocation by letter. Central randomization allowed concealment of allocation from research assistants and GPs until group assignment had occurred. Blinding of participants and EPs was not feasible. Contamination was minimized as the intervention was not delivered at the primary care site and follow-up data collection occurred by mail, with patient-reported survey and pedometer-assessed step counts, so was not influenced by study team members. The data analyst was blinded to group allocation, as surveys were de-identified and did not contain study group information.

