#### Group 1: referral for face-to-face physical activity counseling

Participants randomized to Group 1 attended five face-to-face consultations with an EP over the 13-week intervention period (13 weeks from date of randomization). The initial consultation was approximately 60 minutes, and each follow-up appointment was approximately 30 minutes in duration. The EP consultations were at no cost to participants, and EPs were reimbursed by the research team at a rate of AUD$90 per initial consultation and AUD$55 per follow-up consultation. Consultations occurred at the EPs private practice. The initial consultation comprised an assessment of the participant’s ability to safely undertake physical activity, and the application of behavior change strategies to enhance participation in physical activity, such as goal setting, the identification of barriers to physical activity and collaborative problem-solving to identify strategies to overcome personal barriers to physical activity. At follow-up visits, progress against goals was assessed, new goals set, and any challenges discussed using the same collaborative problem-solving approach. All consultations were patient-centred and tailored to the participant’s physical activity preferences, capability, medical limitations (if present) and personal barriers. Discussion of cognitive and behavioral strategies, derived from SCT, occurred as appropriate to each person’s motivational readiness to change. Beyond the training in patient-centred counseling and behavior change strategies, there was no other attempt to standardize the intervention and its delivery across participants, EPs, or geographic location.

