### Sample size

A sample size of 79 participants per group will provide 90% power to detect a differential increase of 1000 steps per day at 12 months between the two intervention groups and the usual care group at the 5% significance level. This sample size was calculated assuming that the usual care group will increase their average daily step count by 1000 steps, and the standard deviation of 2500 observed in the pilot study. Attrition rates are estimated to be 10% over the twelve month period [60]. This results in a total required sample of 261 (n = 87 per group).

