### Statistical analyses

Baseline data will be summarized as the number of observations, means, standard deviations, medians, minimums and maximums where the data are continuous and as number of observations and frequencies where the data are categorical. The data will be presented separately by treatment group.

The primary endpoint (mean change in daily step counts from baseline to 12 months) will be analyzed using a constrained linear mixed model approach [61], where the outcome in the model is the mean number of steps per day at each time point, but the baseline mean responses for the treatment groups are assumed equal. This approach has been shown to be robust when missing data depend on baseline values [62]. Predictor variables in the model will include fixed effects for group (usual care as reference and group 1: face-to-face, group 2: telephone), time (baseline as reference, 3 months and 12 months) and the interaction between group and time. A subject level random intercept will be included in the model to allow for correlations arising from repeated measures. There may be some variation to this model after checking its underlying assumptions of multivariate normality, linearity and equal variance and clustering. The primary comparison will be between the combined intervention groups (group 1: face-to-face and group 2: telephone) and usual care. A secondary analysis will examine the difference in step counts at 3 months, and if significant differences are found in the primary analysis, will also explore if there are differences between treatment groups (face-to-face and telephone). Sub group analyses will be conducted by sex, BMI category and diagnosed chronic disease versus none. Sensitivity analyses will explore the impact of individual EP, GP clinic, and after removing the steps imputed from self-reported physical activity. The analysis will be conducted on an intention-to-treat basis with alternative methods of accounting for missing data: multiple imputation, and pattern mixture modelling [63].

Process evaluation will be assessed by calculating adherence with intervention (mean number of sessions completed, average time of intervention delivery for face-to-face and telephone counseling sessions). Intervention fidelity will be assessed by coding of EP checklists.

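### The primary model has no exercise physiologist (EP) term although only the intervention arms are nested in EPs, so the standard error is understated if outcomes correlate within EP

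*Protocol article*

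**What the plan says.** The Interventions section says that accredited EPs in private practice deliver the counseling after a five-hour study training session, and that all accredited EPs in the areas were invited. The Group 1 section adds that beyond the training "there was no other attempt to standardize the intervention and its delivery across participants, EPs, or geographic location". Group 2 has one visit and four calls with the same EP. Group 3 has usual GP care and a mailed brochure, with no EP.

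Under Statistical analyses, the primary model has fixed effects for group, time and their interaction. For correlation, "A subject level random intercept will be included in the model". The primary contrast pools Groups 1 and 2 against usual care. The section allows some variation to the model after its assumptions are checked, and clustering is in that list. It does not say which clustering, by what criterion, or what model would follow. EP is then placed among the secondary looks: "Sensitivity analyses will explore the impact of individual EP, GP clinic".

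The Sample size section gives 79 evaluable participants per group for 90% power, using "the standard deviation of 2500 observed in the pilot study". It mentions no design effect. No number of EPs and no ICC appears anywhere in the article.

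**The concern.** Participants who share an EP share that EP's skill and style, which the trial deliberately leaves free to vary. That variation enters the intervention side of the primary contrast and has no counterpart in usual care. Stratifying the second randomization by EP suburb helps to balance EPs between Groups 1 and 2, so EP effects partly cancel when those two are compared. They do not cancel against a group that has no EP.

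A model with only a subject intercept treats all intervention participants as independent of one another. If they are not, the interval for the main result is too narrow. The trial is meant to inform public funding of EP referral in general, so between-EP variation belongs in the uncertainty of its main result.

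**Working it through.** **Inputs from the protocol article.** Difference 1000 steps/day, SD 2500, 5% significance level (sidedness not stated), 79 evaluable per group (Sample size). Allocation is 1:2, usual care to intervention (Randomization and blinding), so the primary contrast compares 79 with 158.

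**The plan's own figure.** Unclustered SE = 2500 × √(1/79 + 1/158) = 344.5 steps, and 1000/344.5 = 2.903.
- One-sided 5%: power = Φ(2.903 − 1.645) = 89.6%, which matches the stated 90%.
- Two-sided 5%: power = Φ(2.903 − 1.960) = 82.7%.

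The stated 90% is therefore reached with no allowance for EP clustering. The sidedness is a separate matter; both readings are carried below.

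**Adding EP clustering in the intervention arms only.** With k EPs of equal size, m = 158/k participants per EP:
- Design effect DE = 1 + (m − 1) × ICC
- SE = 2500 × √(1/79 + DE/158)
- SE ratio = √[(1 + DE/2)/1.5], which does not depend on the SD
- Actual size of a nominal two-sided 5% test = 2 × [1 − Φ(1.96/ratio)]

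Both k and the ICC are assumptions.

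| EPs | ICC | DE | SE | SE ratio | Actual size | Power, two-sided | Power, one-sided |
|---|---|---|---|---|---|---|---|
| any | 0 | 1.00 | 344.5 | 1.00 | 5.0% | 82.7% | 89.6% |
| 20 | 0.01 | 1.07 | 348.4 | 1.01 | 5.3% | 81.9% | 89.0% |
| 12 | 0.02 | 1.24 | 358.2 | 1.04 | 5.9% | 79.7% | 87.4% |
| 12 | 0.03 | 1.37 | 364.8 | 1.06 | 6.4% | 78.3% | 86.3% |
| 12 | 0.05 | 1.61 | 377.8 | 1.10 | 7.4% | 75.4% | 84.2% |
| 8 | 0.05 | 1.94 | 394.7 | 1.15 | 8.7% | 71.7% | 81.3% |

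Worked line, 12 EPs and ICC 0.02: m = 158/12 = 13.17; DE = 1 + 12.17 × 0.02 = 1.243; ratio = √(1.622/1.5) = 1.040; size = 2 × [1 − Φ(1.885)] = 5.9%.

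The middle of the assumed range is the pair of rows with 12 EPs and ICC 0.02 to 0.03. The rows at ICC 0.05 are its upper end. Outside this range the answer moves further: 30 EPs with ICC 0.01 gives ×1.007 and 5.2%, and 5 EPs with ICC 0.10 gives ×1.42 and 16.8%.

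**Would a check of clustering find it?** Suppose the check were a 5% one-way F test of EP among 158 participants. If the true ICC is 0.05, its power is 42% with 8 EPs, 37% with 12 and 29% with 20. It would miss clustering of that size more often than not.

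**The case against.** - **The understatement is conditional.** This stands. At an ICC of zero there is none, and the article gives neither an ICC nor a number of EPs. A reader might infer that the primary standard error is certainly too small, or that only a few EPs took part. The article supports neither: it says only that all accredited EPs in the areas were invited.
- **The plan does not ignore clustering.** This also stands in part. The model may be varied after a check, and an EP analysis is planned. The label sensitivity analysis also ranks the two results, so it would be wrong to say that nothing shows which one is primary. But it ranks first the model without EP.
- **An article may leave such detail to the analysis plan.** That covers the criterion for the check and the degrees-of-freedom method. It does not cover the random-effects structure, which the article does state, with EP assigned elsewhere.
- **The type I error figures need a particular null.** This stands. Participants are individually randomized. If counseling changes nobody's activity, EP skill cannot create correlation. The inflated sizes apply where EPs have real, differing effects that average zero. Otherwise the issue is interval width, and whether the inference is to these EPs or to EPs in general.
- **The remedy has its own difficulties.** Participants named preferred suburbs, so EP is entangled with area. An EP term fitted only in the intervention arms may absorb area variation that also exists in usual care. With few EPs the variance may be poorly estimated or fall at zero. Only the EP's suburb location is documented as a stratum, not an individual EP. These points shape the fix but do not remove the need for it.

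**Conclusion.** The point holds in conditional form. The primary contrast is partially nested, and the stated primary model leaves out the one source of correlation that the design places on one side only. An undefined check and a sensitivity analysis are weak substitutes.

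Over 8 to 20 EPs and ICC 0.01 to 0.05, the standard error is understated by a factor of 1.01 to 1.15. A nominal two-sided 5% test runs at about 5.3% to 8.7%, with central values near 1.04 to 1.06 and 5.9% to 6.4%. The low end is negligible and the high end is not. These figures rest on the assumed EP number and ICC, EPs of equal size, a normal approximation and, for the test size, EP effects that differ but average zero. The change is worth making because it is cheap, not because serious bias has been shown.

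**What to change.** Prespecify in the primary model a random EP effect for intervention participants at the 3- and 12-month visits only, with none at baseline and none for usual care. Use Satterthwaite or Kenward-Roger degrees of freedom. Make the model without the EP term the sensitivity analysis. GP clinic can stay a sensitivity analysis, because participants were individually randomized and clinics are therefore crossed with arm.

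Keep non-attenders in the analysis under the EP they were referred to or, if no individual EP was assigned, under the EP suburb location used as the stratum at randomization. State in advance what is done if the EP variance is estimated as zero.

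The cost is a paragraph of analysis-plan text and one variance component. An EP analysis is already planned and EPs return a checklist for every consultation, so little or no new data collection is needed. The drawbacks are a somewhat wider interval, an EP variance that may be imprecise with few EPs, and some area variation that may be absorbed into it.

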### Economic analysis

Economic analysis from the health funder perspective will form part of this trial. Costs of the intervention will be derived from the time spent by the EPs on consultations in person and by phone, and on record keeping, and will include the time spent by the GP making the referral. Utility will be derived from the AQoL responses transformed into Quality Adjusted Life Years (QALYs) and the incremental cost per QALY will be calculated.

### Secondary analyses

i.An exploration of whether change in physical activity behavior results in spontaneous change in other health behaviors (smoking, alcohol consumption).ii.An examination of the predictors of participants who adhere with the NewCOACH intervention.iii.Mediation and moderation analyses to identify factors associated with physical activity behavior change.iv.An exploration of whether there is any difference in intervention efficacy between people who receive their preferred study group allocation and those who do not.v.The impact of the physical activity intervention on quality of life, depression, and fatigue.vi.Relationships between changes in step count and changes in accelerometer-derived sitting time.

### Ethics

The study has been approved by the University of Newcastle’s Human Research Ethics Committee (H-2011-0063).

## Discussion

The NewCOACH study is a three-arm pragmatic randomized trial that aims to determine the efficacy of GP referral of insufficiently active patients (regardless of their chronic disease status) for physical activity counseling (either face-to-face or predominately via telephone) by exercise specialists, based on patients’ objectively assessed physical activity levels, compared with usual care. If the trial is efficacious, the equivalence and cost-effectiveness of face-to-face counseling versus telephone counseling will be assessed.

Strengths of this study include the pragmatic design, the use of an objective measure of physical activity, the use of qualified exercise specialists (EPs) to deliver the theory-based behavior change counseling, and the 12 month follow-up to assess maintenance of behavior change. Limitations of the study include that only a sub-sample will provide accelerometer data.

If the physical activity counseling is efficacious, this will have implications for the design of future exercise referral schemes and EP funding models both in Australia and internationally. If the trial demonstrates that referral to an EP for coaching is an effective way to get people more active, it will be very attractive to GPs to make greater use of CDM pathways. Current funding legislation in Australia restricts CDM to those with an existing chronic disease [64]. If improvements in physical activity can be demonstrated for previously inactive but otherwise healthy adults in this trial, this will provide support for expansion in the eligibility criteria for the Medicare allied health initiative to include insufficiently active patients who do not have a chronic condition. This would be a significant shift away from just treatment of disease, and would acknowledge the role of allied health professionals in preventing disease in partnership with primary care clinicians. In addition, Medicare funding currently only recognizes face-to-face consultations. Evidence that telephone coaching is equally or more effective could lead to the funding of EP services for telephone delivery which would increase the reach and flexibility of this service.

## Abbreviations

GPs: General practitioners
CDM: Chronic disease management
EP: Exercise physiologist
ESSA: Exercise and Sports Science Australia
SCT: Social cognitive theory
ITT: Intention to treat
QALY: Quality adjusted life years
